## Abstract

**Background:**

Internationally, the rate of child loss during pregnancy or birth remains high. This has not only physical but also psychological implications for the parents. While much is known today about the medium- and long-term impact of such a loss, very little research is available on the experience and needs before and during intrauterine or perinatal loss. In addition, healthcare professionals feel insecure and unprepared when dealing with this specific group, which also has a lasting impact on those affected.

**Aim:**

To develop recommendations for healthcare professionals on how to deal with families before and during the intrauterine or perinatal loss of their child.

**Methods:**

An explorative, sequential and participatory mixed-methods study will be conducted. Along its design, an affected mother is involved throughout the entire study. In detail, workshops, focus groups and narrative interviews with parents are planned. We will include parents who have lost their child during pregnancy or birth within the last 12 months and live in Germany, Austria or Switzerland. The results of the research are then translated into recommendations, which are reviewed and confirmed together with affected parents in a Delphi survey. Finally, a guideline for healthcare professionals will be developed.

**Discussion:**

The co-creative design of this study enables the experience-based development of recommendations for healthcare professionals.

**Clinical trial registration:**

The study was registered in the National Library of Medicine on January 13^th^, 2025 with the unique ClinicalTrials.gov identifier NCT06771661 (https://clinicaltrials.gov/study/NCT06771661).

## Background

### Introduction

Worldwide, the number of stillbirths is estimated at about 2.6 million per year [1, 2]. While up to 26.4 stillbirths occur for every 1,000 live births in developing countries [3], in the USA, for example, the rate is significantly lower at 6 per 1,000 [4, 5]. Despite this difference, the rate of stillbirths remains high [4, 6] and still increases in some cases [7]. In addition, the risk of miscarriage also continues to stay on a high level, especially in the first trimester. Across all pregnancies, the rate of miscarriages is at 15% [8].

Today, many risk factors have been investigated that induce the pathological course of pregnancy. In addition to advanced age, ethnicity, maternal hypertension and malnutrition, the main factors for child loss during pregnancy are growth disorders, infections, cervical diseases, mental illnesses and substance abuse [5, 8–12]. Nevertheless, in over 60% of cases, the etiology of the child’s death remains unknown [13].

However, child loss during pregnancy not only has medical implications, but also a significant impact on the families affected. Research from the last 20 years has shown that a lack of support during pregnancy loss and insufficient efforts to deal with this traumatic event can have serious psychological and physical consequences for the parents [14–17]. In order to prevent these consequences, various assessments and interventions have already been empirically investigated [18–20].

### Problem definition

While much is known about the long-term effects of the loss of a child, a significant research gap is also evident at this point. Families express various needs during the intrauterine phase and their pregnancy loss (e.g. [21], ), but these are still not described and analyzed in a differentiated way. The experience before stillbirth (intrauterine phase) and during stillbirth (birth itself) is also not depicted in the literature, in contrast to the aftermath. This also means that there is a lack of explanations for the targeted development of interventions and the origin of long-term effects on the parents.

A closer look at international medical, midwifery and nursing literature also reveals that neither guidelines nor studies and textbooks contain recommendations on how to deal with parents during stillbirth. This is also evident in studies among healthcare professionals (HCPs). They often feel insecure when dealing with parents during stillbirth [22] and are confronted with the ambiguity of the situation in which they have to mediate between the parents and their needs on the one hand and the healthcare system, the facilities and their aims on the other [22]. Various challenges such as their own emotions and lack of knowledge influence the work of HCPs [23] and lead to parents being avoided and stigmatized [22].

HCPs state that they have little or no training in caring for this specific patient cohort [22]. They suffer during the care themselves [22] and experience stress, especially when they have little experience or knowledge and perceive the missed care or inadequate staff performance [24]. HCPs are longing for an in-depth understanding, multi-professional training and sensitization tailored specifically to this patient cohort [23].

This situation results in inadequate care for the parents. They feel poorly informed and have few opportunities to communicate with HCPs [25, 26]. Finding themselves in a highly challenging situation with special needs [27], parents often feel overlooked and experience indifferent or dismissive HCPs, which leads to anxiety and frustration [28]. These experiences along with the lack of interaction with HCPs shapes the parents not just temporarily, but for years [23, 26, 27].

Parents are unable to assess and properly understand their own situation and the little information available [28], which can result in their (gradual) social withdrawal, psychological problems and an unhealthy lifestyle as a coping strategy [28, 29]. In various countries, there is also a lack of follow-up care, guidance and bereavement support beyond the acute inpatient stay [26, 30].

### Aim and research question

Based on the problem definition, this study aims to develop recommendations for HCPs on how to deal specifically with families before and during the intrauterine or perinatal loss of their child. To this end, two research questions were formulated that are to be answered by the study:How do parents experience the intrauterine or perinatal loss of their child?What needs and requirements arise for families experiencing intrauterine or perinatal loss of their child?

## Methods

In order to answer the underlying research questions and achieve the formulated aim, an explorative-sequential mixed methods study will be conducted [31]. The study is designed as participatory research and, in the sense of a co-creative design, will not only survey affected parents in three central survey steps, but also actively involve them in the development of the study design and the progress of the study. To enhance transparency over the study course, we registered our study in the National Library of Medicine (https://clinicaltrials.gov/study/NCT06771661) with the clinical trial number NCT06771661.

The reporting of this study protocol follows the ‘Standard Protocol Items: Recommendations for Interventional Trials’ (SPIRIT) guideline [32, 33], as no other reporting guideline could be identified for study protocols. Nevertheless, the SPIRIT guideline is designed for interventional trials, which is why not all recommended items fit for our study and will therefore be excluded.

### Study setting

In order to de-pathologize stillbirth, none of the data collection will take place in the hospital setting. The workshops, focus groups and the ensuing Delphi method will be set up on the research institutions involved. The narrative interviews will be conducted at the parents’ homes or at a neutral location of their choice.

### Eligibility criteria

As recommended for primarily qualitative studies [34, 35], our eligibility criteria is based on the PICo design (**P**opulation, Phenomenon of **I**nterest, **Co**ntext). The population of interest includes parents (mothers and fathers) after stillbirth who are at least 18 years old, understand and speak German and live in Germany, Austria or Switzerland. They must also have legal capacity and participate in the study voluntarily.

The phenomenon of interest encompasses the experience of the parents as well as the needs and requirements of the family (mothers, fathers, siblings). In order to avoid possible recall bias [36, 37], the intrauterine or perinatal loss must not have occurred more than twelve months prior to data collection.

The context is stillbirth, which in this study is defined as the birth of an intrauterine deceased embryo or fetus, regardless of its age. In addition, we included parents after a (largely) physiological birth with perinatal death of the newborn child. In terms of the time period, we deliberately did not set any posterior limits as eligibility criteria but rather focused on a qualitative definition by the participants themselves. When recruiting participants, the phrase ‘death of the child during pregnancy or birth’ is therefore used. We deliberately did not distinguish between early or late loss during recruitment, as we want to uncover both potential differences and similarities in their experiences throughout the study. Parents relating to the phenomenon are eligible to participate in the study.

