### Recruitment

We will primarily recruit participants for our study using a digital snowball principle. Therefore, a landing page was set up via the primary affiliation of the authors, on which all relevant study-information can be found (https://www.th-deg.de/sterneneltern). The university’s marketing service creates advertising materials. These will be distributed to relevant healthcare institutions via email or direct message with a request for forwarding. The study will also be publicized on social media (Facebook, Instagram, Twitter) via the university’s institutional channel. In addition, the aforementioned organizations will be asked to advertise the study on their own social media channels. In case of only a few participants being recruited via this approach, information material will be sent to midwife practices, birth centers, gynecologists, obstetrics departments in hospitals and support groups.

If a potential participant contacts the research team, an initial preliminary telephone interview takes place in which the intention of the study is explained. In addition, background information is queried and it is checked whether the participants actually correspond to the required eligibility criteria.

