### Data privacy management

Over the course of the study, we will collect several personal and health-related data from the participants. Specifically, we will ask about their age, gender and the country of residence. We also want to know when the loss of the child took place (month, year) and whether the child died during pregnancy or birth. Finally, we will ask whether the affected parents gave birth to other children before and after the stillbirth. We deliberately refrain from collecting further personal data (school-leaving qualifications, education, place of residence, financial situation, etc.). This data does not add any value and in no way contributes to answering our research questions.

Nevertheless, we will collect several sensitive data that are particularly in need of protection. To secure this data, we have gone through a data privacy management process with the data privacy officers of the authors’ primary affiliation and jointly developed a strategy. The final results are publicly available (https://dpm.th-deg.de/infoduties/KmsaRM).

Consequently, all participants must sign an informed consent before participating in the study. In addition, they can withdraw from their participation at any time and are able to request the deletion of all contributions. All data collected (on paper, as audio, as images) is pseudonymized and stored digitally in the primary affiliation’s double-protected cloud. A key list is created for decoding, which is locked away as a printed version. Only the authors of this study have access to the pseudonymized data. All of them have signed a confidentiality agreement and guarantee that no information will be shared with third parties.

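### The recruitment phrase ends at birth although parents of a newborn who died perinatally are eligible, so this group may be under-recruited and hard to identify in the data

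*Protocol article*

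**What the plan says.** The Eligibility criteria section defines the context as stillbirth, meaning the birth of an embryo or fetus that died in the womb at whatever age. It then adds a second group: "In addition, we included parents after a (largely) physiological birth with perinatal death of the newborn child". On timing it states that "we deliberately did not set any posterior limits as eligibility criteria but rather focused on a qualitative definition by the participants themselves", and it draws the recruitment wording from this: "When recruiting participants, the phrase ‘death of the child during pregnancy or birth’ is therefore used". The section closes with a rule of self-identification: "Parents relating to the phenomenon are eligible to participate in the study".

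The Recruitment section describes a landing page, advertising material passed on by healthcare institutions, and social media posts. Once a parent has made contact, a telephone interview follows in which "it is checked whether the participants actually correspond to the required eligibility criteria".

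The abstract states inclusion in the narrower terms: "We will include parents who have lost their child during pregnancy or birth within the last 12 months". The Data privacy management section lists what will be recorded about each participant. On the timing of the death, beyond month and year, it lists "whether the child died during pregnancy or birth".

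**The concern.** The phrase is presented as following from a wish to leave the time frame open, yet its own end point is birth. A parent whose child was born alive and died soon afterwards belongs to the group that the eligibility text adds on purpose, but is not named in the invitation.

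Two things are at stake. The first is selection: such parents may decide that the study is not meant for them. The second is classification: if they do take part, the timing item as described has no evident place for their loss. The aim and both research questions cover intrauterine or perinatal loss, and the recommendations for healthcare professionals are to have the same scope. If one part of that scope is thinly represented, or cannot be picked out in the data, readers could not tell how far the recommendations rest on the experience of these parents.

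**Working it through.** No arithmetic applies. The check is a comparison of texts.

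**1. Who is eligible.** The Eligibility criteria section names two groups. The stillbirth definition covers death in the womb. The second group is added separately and its child is called a newborn. The natural reading is that the second group includes children who were alive at birth and died afterwards, since deaths in the womb are already covered by the first.

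**2. What the invitation names.** The recruitment phrase names death in pregnancy and death at birth. Taken literally, it covers the first group in full. It covers the second only as far as the death counts as part of the birth itself.

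**3. Whether the stated reason supports the phrase.** The sentence before it says that "we deliberately did not set any posterior limits as eligibility criteria", and the phrase is said to follow from that. A phrase whose last named event is birth does not express the absence of a later limit. The reason and the wording point in different directions.

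**4. Whether the same wording recurs.**

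| Place in the protocol article | Death in pregnancy named | Death at birth named | Death after birth named |
|---|---|---|---|
| Eligibility criteria, population and context | yes | yes | yes, through the newborn sentence |
| Eligibility criteria, recruitment phrase | yes | yes | no |
| Abstract, inclusion statement | yes | yes | no |
| World café, second-station question on media coverage | yes | yes | no |
| Focus groups, opening question | yes | yes | no |
| Narrative interviews, opening prompt | yes | yes | no |
| Data privacy management, timing item | yes | yes | no |

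The workshop's warm-up question about the loss of the child carries no time limit, so not every prompt is affected.

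**5. Whether a later step corrects it.** The telephone interview applies the eligibility criteria, which admit the group. It takes place only after a parent has contacted the team, so it can correct a misunderstanding in a parent who calls but cannot reach one who read the invitation and moved on. The self-identification rule has the same limit: it works only if the parent recognises the loss in the wording offered.

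**6. Whether other recorded items identify the group.** The remaining items are age, gender, country of residence, month and year of the loss, and other children. None of them shows whether the child died before, during or after birth. An interview may reveal it, but the structured data as described would not.

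**The case against.** The strongest reply is that the phrase is an invitation and not an exclusion criterion. Eligibility rests on self-identification and on criteria that expressly include this group, and the telephone call applies those criteria. This stands. A reader might infer that parents of newborns who died after birth are screened out, that almost none will be enrolled, or that they will be largely absent from every phase. The documents support none of this. Some parents will read birth broadly, and those who call would be admitted. The planned sample sizes do not help either: they count places, say nothing about the share of such losses, and participants may overlap between phases.

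It can also be said that the landing page and advertising texts are not shown and are presumably in German, so their full content is unknown. That is fair, and it limits how firmly one can predict who responds. But the protocol chooses to state the phrase that recruitment uses, and that statement can be judged.

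Third, the timing item is a prose summary in a privacy section, not a form, and no planned analysis is stratified by it. So it cannot be said that such losses will be recorded wrongly, only that the described item leaves no clear place for them. The protocol does want to uncover differences and similarities between kinds of loss, so being able to identify them has some value.

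Finally, perinatal is not defined, the research gap is framed around the time before and during stillbirth, and the remark on posterior limits stands close to the decision not to separate early from late loss. The authors may have meant birth in a wide sense. If so, the wording needs to say so, because a parent reading the invitation does not have that context.

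**Conclusion.** The point holds as a mismatch between stated eligibility and stated recruitment wording, repeated in the prompts and the timing item. Its consequence is a risk that an eligible group is under-recruited and that those who enrol cannot be identified from the recorded timing. The size of this risk cannot be estimated, because the documents give neither the share of deaths after birth among eligible losses nor any indication of how parents read the phrase.

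The conclusion rests on two assumptions: that the newborn sentence is meant to include children who were alive at birth, and that the unseen materials follow the phrase that the protocol states. If the landing page and flyers already name death after birth, the selection part falls away and only the prompts and the timing item remain to be aligned. The matter should be corrected because the change is small and serves the authors' own intention, but it does not call the design into question.

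**What to change.** Extend the recruitment phrase so that it names death in pregnancy, during birth or shortly after birth. Use that wording consistently on the landing page, in the advertising material, in the abstract's inclusion statement, and in the World Café, focus-group and narrative prompts. Give the timing item three options: before, during and after birth. Age at death is not needed; collecting it would run against the deliberate limit on personal data in the Data privacy management section.

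If losses after birth are not intended, remove the newborn sentence from the Eligibility criteria and limit the aim, research questions and recommendations to intrauterine and intrapartum loss.

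The first route costs a minor update of the study materials and the screening questions, to be aligned with what the ethics committee and the data privacy officers have seen, and may give a slightly more mixed sample. The second costs scope: the guideline could no longer claim to cover the whole of perinatal loss.

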### Sample size

In accordance with the recommendations for qualitative interviews [38–43], we estimated 25–30 participants for the workshops and focus groups. For each workshop day and focus group, eight to ten participants should be recruited. For the narrative interviews, which focus on in-depth content rather than quantity, we plan to recruit eight to twelve participants. In order to subsequently enable a sufficient Delphi process in which every person has their say, we will recruit twelve to 16 participants [44–46].

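### Early and late loss are left unsorted at recruitment so that differences can emerge, but nothing secures several parents of each kind in the 8–12 interviews or the Delphi panel

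*Protocol article*

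**What the plan says.** The Eligibility criteria section admits a wide range of losses. Stillbirth is "defined as the birth of an intrauterine deceased embryo or fetus, regardless of its age", and in addition "we included parents after a (largely) physiological birth with perinatal death of the newborn child". On timing it states: "We deliberately did not distinguish between early or late loss during recruitment, as we want to uncover both potential differences and similarities". These differences are to be looked for in parents' experiences over the course of the study.

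The Sample size section fixes totals only. The workshops are to hold 25 to 30 parents in all, with 8 to 10 on each day, and the Delphi panel 12 to 16. The interviews have the smallest total: "For the narrative interviews, which focus on in-depth content rather than quantity, we plan to recruit eight to twelve participants".

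Recruitment is by digital snowball. A preliminary telephone call collects background information, and "it is checked whether the participants actually correspond to the required eligibility criteria". The one selection preference in the article is under Methodological framework: if numbers allow, interviewees should not already have taken part in a focus group.

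The Narrative interviews section assigns the first research question, on experience, to these interviews. The list of data items under Data privacy management has the month and year of the loss and whether the child died in pregnancy or at birth. Gestational age at loss is not on it.

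**The concern.** To see whether early and late loss are experienced differently, one needs several parents of each kind in the sample that addresses experience. Not sorting by timing keeps the door open to both, but does not bring both in. The totals carry no minimum, the telephone call is described only as a background and eligibility check, and the one selection preference concerns repeat participation.

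If the interviews contain none or one of a kind, a difference cannot be recognised, and an apparent similarity may reflect only who volunteered. The Delphi panel could then endorse recommendations meant for all intrauterine and perinatal losses with hardly any parent of one kind among its members.

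**Working it through.** **Inputs from the article.** Workshops and focus groups 25–30 (three days of 8 to 10 each); interviews 8–12; Delphi 12–16.

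**Input not in the article.** The share p of the less common kind of loss among volunteers. It is treated as an assumption and varied.

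**Check of the stated total.** 3 × 8 = 24 and 3 × 10 = 30, against the stated 25–30. The figures agree closely enough.

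**Formula.** With n independent participants, the chance of none or one of the less common kind is P(X ≤ 1) = (1 − p)^n + n·p·(1 − p)^(n − 1).

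**Worked examples at p = 0.20.**
- n = 8: 0.8^8 + 8 × 0.2 × 0.8^7 = 0.168 + 0.336 = 0.503.
- n = 12: 0.8^12 + 12 × 0.2 × 0.8^11 = 0.069 + 0.206 = 0.275 (0.2749 before rounding, hence 27%).

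**Results, P(X ≤ 1):**

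| Sample | p = 10% | p = 20% | p = 30% | p = 50% |
|---|---|---|---|---|
| Interviews, n = 8 | 81.3% | 50.3% | 25.5% | 3.5% |
| Interviews or Delphi, n = 12 | 65.9% | 27.5% | 8.5% | 0.3% |
| Delphi, n = 16 | 51.5% | 14.1% | 2.6% | <0.1% |
| Workshops pooled, n = 25 | 27.1% | 2.7% | 0.2% | <0.1% |
| Workshops pooled, n = 30 | 18.4% | 1.1% | <0.1% | <0.1% |

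**Share needed to hold P(X ≤ 1) at 5%.** Solving for p gives 47% for n = 8, 34% for n = 12, 26% for n = 16, 18% for n = 25 and 15% for n = 30. So the pooled workshops are fairly safe unless one kind is below about 15–18% of volunteers. Eight interviews are safe only if the split is close to even.

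**Independence.** This assumption probably flatters the plan. Snowball recruitment tends to bring in similar parents, and the Narrative interviews section allows both parents of one child to be interviewed, so two participants may represent a single loss.

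**The case against.** The best defence is that this is open exploratory work. Neither research question compares early with late loss, and leaving participants unsorted so that patterns can emerge is a coherent rationale. That stands as a reason for broad eligibility and a single advertisement. It does not supply a way of getting both kinds into a sample of eight.

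A second defence is pooling. Workshops and interviews together hold 25 + 8 = 33 to 30 + 12 = 42 parents. At a 20% share the chance of at most one is then 0.6% to 0.1%; at 10% it is 14% to 7%. This is right for the study as a whole, and it confines the concern to the smaller phases. It does not remove it, because the question on experience is assigned to the interviews, while the focus groups are assigned the question on needs. It is also fair that the Delphi rates recommendations and does not explore experience, so its exposure is secondary.

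Third, the article does not say how places are allotted. It speaks of selecting interviewees and of taking gaps from the first phase into the interviews, so there is room to respond. That room is not tied to kind of loss.

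Stronger readings are tempting but not supported:
- A reader might take the Introduction's miscarriage figure ("Across all pregnancies, the rate of miscarriages is at 15" per cent) and its stillbirth rate of 6 per 1,000, and infer that early losses outnumber late ones 0.15/0.006 = 25 to 1, so that late loss would usually be missing. The two rates have different denominators, the second is a US figure although participants live in Germany, Austria or Switzerland, perinatal deaths are left out, and volunteers need not mirror incidence.
- A reader might infer that one kind will be scarce in all phases at once. At a 20% share that chance is 0.4% or less; it becomes likely only near 5%.
- A reader might infer that places go to volunteers strictly in order of arrival. The article does not say so.

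**Conclusion.** The concern holds in a limited form. Uncovering differences is the stated reason for not distinguishing time of loss, and no selection step described in the article secures both kinds where the samples are smallest. The exposure lies mainly in the interviews, less in the Delphi panel, and little in the pooled workshops.

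Its size depends on a volunteer mix that the article does not give. For 8 to 12 interviews, the chance of at most one parent of the less common kind runs from 81–66% at a 10% share, through 50–27% at 20%, to about 4% or less for a given kind at an even split. This does not show that the sample will be unbalanced. It shows that balance is unsecured and that securing it is cheap. The figures assume independent participants, which is probably optimistic.

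**What to change.** Keep the broad eligibility, the advertisement wording and the planned totals. Then:

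1. Ask at the existing telephone call for gestational age at loss, or whether the child died at or around birth, and add this item to the list under Data privacy management.
2. State in advance the cut-off between early loss and late or perinatal loss. The choice is the team's.
3. Select interviewees purposively, and Delphi members where possible, so that each of the two kinds is represented by several parents. Set no quota per workshop day: it could leave places empty, and the pooled workshops need it least.
4. If a kind still ends with none or one case, make no early-versus-late statement and limit the scope of the recommendations accordingly.

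The sentence on timing could become: *We do not restrict eligibility by time of loss, but select interviewees, and where possible Delphi members, so that early loss and late or perinatal loss are each represented by several parents.*

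The cost is one more data item and somewhat slower filling of interview and Delphi places.
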